## **6.0 Research Hypotheses**

1. There is a difference between the effects of DD-10, S-10, and S-0 pressure garment on motor control as measured by Fugl-Meyer Assessment of Upper Extremity

(Kaufman et al.) among stroke patients during 8 weeks of application.

2. There is a difference between the effects of DD-10, S-10, and S-0 pressure garment on dexterity as measured by Box and Block Test (BBT) among stroke patients during 8 weeks of application.

3. There is a difference between the effects of DD-10, S-10, and S-0 pressure garment on muscle tone as measured by Modified Ashworth Scale (MAS) among stroke patients during 8 weeks of application.

4. There is a difference between the effects of DD-10, S-10, and S-0 pressure garment on pain as measured by Visual Analogue Scale (Venckūnas et al.) among stroke patients during 8 weeks of application.

5. There is a difference between the effects of DD-10, S-10, and S-0 pressure garment on self-perceived upper extremity function as measured by Disabilities of Arm, Shoulder and Hand (DASH) among stroke patients during 8 weeks of application.

6. There is a difference between the effects of DD-10, S-10, and S-0 pressure garment on quality of life as measured by 36 Item Short Health Survey (SF-36) among stroke patients during 8 weeks of application.

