##### **9.1.2.1 Inclusion and Exclusion Criteria**

Inclusion criteria:

1. Between 18 and 80 years of age
2. Within 1 – 12 months of ischemic or haemorrhagic stroke
3. First onset resulting in hemiparesis of a limb with Brunnstrom Recovery Stage (BRS)

of 3, 4 or 5 (Naghdi et al. 2010)

4. Modified Ashworth Scale (MAS) with scores of less than or equal to level 2 for elbow, wrist, and hand muscle tone in the affected upper extremity (Harb & Kishner 2022)

5. Able to understand instruction

Exclusion criteria:

1. Serious cardiovascular or respiratory diseases
2. Skin lesions, infections or other skin problems
3. Serious circulatory problems such as deep vein thrombosis
4. Allergies or significant discomfort to pressure garment materials
5. Upper extremity fractures or severe joint problems
6. Severe cognitive impairment with Saint Louis University Mental Status (SLUMs) scores equal to or less than 27 (above high school level of education)/25 (below high school level of education).

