#### **9.1.2.3 Sample Size Calculation**

Sample size was calculated using G\*Power 3.1. Assuming that the data is normally distributed, this study will use mixed model ANOVA to compare differences between

the effects of DD-10, S-10, and S-0 pressure garment on sensorimotor functions and quality of life among stroke patients at three different time points during the 8 weeks of application. With small to medium effect size,  $f$  of 0.125, power of 0.8,  $\alpha$  error of 0.05, three groups, and three measurements, the total sample size needed will be 132, as shown in Figure 4. With 44 people in each group and taking into account the 20 % dropout rate, by using the formula:  $N = n/(1-d)$ , i.e.,  $44/(1-0.2) = 55$ , there will be a total of 55 people in each group. Thus, the final sample size will be 165 patients ( $n$ : DD-10 Group = 55; S-10 Group = 55; S-0 Group = 55).

[figure not shown]

Figure 4. Sample Size Calculation

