#### **9.1.4.3 Assessment Instruments**

The assessment instruments include Fugl-Mayer Assessment of Upper Extremity as a primary outcome measure; Box and Block Test, Modified Ashworth Scale, Visual Analogue Scale, and Disabilities of Arm, Shoulder and Hand as secondary outcome measures; and Brunnstrom Recovery Stage and Saint Louis University Mental Status as screening measures.

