#### **9.1.4.3.5 Modified Ashworth Scale (Appendix F) – Screening and Secondary Outcome Measure**

The Ashworth Score is a measure for assessing muscle tone and is commonly used in the assessment of patients with neurological disorders, particularly when assessing patients with spastic paralysis (Lee et al. 1989). The Modified Ashworth Score (MAS) is a modification of the Ashworth score. It is also a method used to assess muscle tone or muscle spasticity, and is primarily used in patients with central neurological disorders, especially stroke patients (Harb & Kishner 2022). It is more detailed and systematic in its assessment of muscle spasticity than the traditional Ashworth score and still uses a scale of 0 to 4, where 0 indicates no spasticity and 4 indicates severe spasticity, with each scale being clearly described (Blackburn et al. 2002).

The reliability and validity of the Modified Ashworth English version was relatively high with ICC=0.874-0.973 (Akpınar et al. 2017). The Chinese version had ICC=0.58-0.89 and highly correlated with BI (Barthel Index) ( $r=0.816$  to  $1.000$ ,  $p<0.01$ ) & with the motor component of Functional Independence Measure (M-FIM) total score ( $r= 0.935$  to  $0.981$ ,  $p<0.01$ ), indicating good reliability and validity (Li et al. 2014).

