### **9.1.6 Data Analysis**

Data will be analysed using SPSS 26.0 using Intention-to-treat (ITT) analysis. ITT analysis, which aims to minimize bias and maintain random allocation of study participants (Gupta 2011), is suitable to be used when there are shedding participants. Its key idea is to analyse the group to which the participant belongs in that initial allocation, regardless of whether they completed the study or received the intended intervention. In clinical trials, participants may drop out, refuse intervention, or deviate from the study protocol. The ITT analysis includes all participants regardless of whether they completed the study or followed the treatment plan. This helps prevent shedding bias, which may occur if only completers are analysed (Mccoy 2017). The study will use a imputation method, such as, Last Observation Carried Forward (LOCF) (Shao & Zhong 2003) or mean imputation (Jadhav et al. 2019), or multiple imputation (Austin et al. 2021), this will probably depend on the requirements of the data.

Both descriptive and inferential statistics will be used. Frequencies, means, and medians will be used to describe the demographic data (Fisher & Marshall 2009). A mixed model ANOVA to compare the outcome measures.

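### The mixed ANOVA planned for every outcome makes the Modified Ashworth result depend on how grades are numbered; a baseline-adjusted ordinal model avoids this and is more sensitive, mainly through the baseline adjustment

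*Protocol*

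**What the plan says.** Protocol section 9.1.6 (Data Analysis) gives one inferential method: "A mixed model ANOVA to compare the outcome measures". Section 9.1.2.3 (Sample Size Calculation) states its basis and scope: "Assuming that the data is normally distributed, this study will use mixed model ANOVA to compare differences between" the three garments on sensorimotor function and quality of life at three time points. Section 8.0 counts MAS among the sensorimotor measures.

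MAS has its own hypothesis in section 6.0, on "muscle tone as measured by Modified Ashworth Scale (MAS) among stroke patients during 8 weeks of application", and is listed as secondary in section 9.1.4.3: "Box and Block Test, Modified Ashworth Scale, Visual Analogue Scale, and Disabilities of Arm, Shoulder and Hand as secondary outcome measures". Section 9.1.4.3.5 describes a scale that "still uses a scale of 0 to 4, where 0 indicates no spasticity and 4 indicates severe spasticity". Entry (section 9.1.2.1) requires patients "with scores of less than or equal to level 2 for elbow, wrist, and hand muscle tone in the affected upper extremity", with no minimum grade.

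The protocol names no ordinal or rank method. It gives no numeric code for MAS grades and does not say which of the three joints, or what combination of them, is analysed.

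**The concern.** MAS grades are ordered categories. A mixed ANOVA needs them as numbers and treats equal numerical steps as equal changes in tone. Nothing in the protocol supports that spacing. With entry capped at level 2, only the lowest few grades per joint can occur at baseline, so the data are coarse and bounded below at 0.

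Two things follow for Hypothesis 3:

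- The verdict on muscle tone can turn on a coding choice that the protocol does not fix.
- An omnibus group-by-time test on three visits does not adjust for the baseline grade and spreads its attention over all visits. This is a matter of contrast and adjustment, not of ordinality, and should be kept apart from the first.

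Muscle tone matters here. The introduction presents reduced tone as a reason for using the garment, and the earlier stroke trial it cites found no difference in arm spasticity.

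**Working it through.** **1. The plan's own figure, and which test it implies.** Inputs from section 9.1.2.3: f = 0.125, alpha 0.05, power 0.8, three groups (k), three measurements (m). Assumed, because the text does not state them: correlation between visits rho = 0.5 and no sphericity correction.

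- Interaction: lambda = f² × N × m / (1 − rho) = 0.015625 × 132 × 3 / 0.5 = 12.375.
- Degrees of freedom: (k−1)(m−1) = 4 and (N−k)(m−1) = 129 × 2 = 258.
- Power = 0.808, and 132 is the smallest multiple of 3 that reaches 0.80.
- At the same inputs the within-subject test would need 105 and the between-group test 417. The stated 132 therefore matches the group-by-time interaction.
- Dropout: 44 / (1 − 0.2) = 55 per group, 165 in total.

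The figure reproduces, and the interaction is taken below as the planned test.

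**2. Why coding matters.** Assume an intermediate grade between 1 and 2 (Appendix F is not shown). Coding the four lowest grades 0, 1, 2, 3 makes a fall from grade 2 to intermediate count 1, the same as a fall from grade 1 to 0. Coding them 0, 1, 1.5, 2 makes the first count 0.5 and the second 1. Merging the intermediate grade with 1 makes a fall from intermediate to 1 count 0.

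**3. Simulated trials.** The documents give no MAS distribution or effect, so all of the following is assumed: one grade per patient, 44 per arm, and a latent normal variable cut into grades, with baseline at or below grade 2.

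- Set A: baseline 25/30/25/20% over 0/1/intermediate/2, correlation 0.6, Week 8 effect 0.5 SD in one arm or 0/0.25/0.5 SD across arms; 600 trials for power, 3,000 for coding changes.
- Set B: correlation 0.7, effects 0/0.25/0.5 SD at Week 8 and half that at Week 4, baseline mid-scale or near the floor; 900 trials.

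Power at 0.05 (codings: equal steps / intermediate = 1.5 / intermediate merged with 1):

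| Scenario | Mixed ANOVA interaction | Same test on ranks | Week 8 linear ANCOVA | Week 8 proportional odds, baseline-adjusted |
|---|---|---|---|---|
| A, one arm | 0.438 / 0.420 / – | – | 0.702 / 0.700 / – | 0.733 |
| A, graded | 0.355 / 0.330 / – | – | 0.575 / 0.578 / – | 0.593 |
| B, mid-scale | 0.453 / 0.498 / 0.354 | 0.477 | 0.702 / 0.673 / 0.563 | 0.719 |
| B, near floor | 0.289 / 0.314 / 0.263 | 0.317 | 0.583 / 0.559 / 0.486 | 0.602 |

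A smaller run (150 trials, correlation 0.6, graded effects) gave 0.42-0.45, 0.63-0.65 and 0.65 for mixed ANOVA, ANCOVA and proportional odds. The Monte Carlo standard error is about 0.02 at 600 trials.

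**4. Splitting the power gap (equal-step coding).**

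- ANCOVA minus mixed ANOVA: 0.702 − 0.438 = 0.264; 0.575 − 0.355 = 0.220; 0.702 − 0.453 = 0.249; 0.583 − 0.289 = 0.294.
- Proportional odds minus ANCOVA: 0.733 − 0.702 = 0.031; 0.593 − 0.575 = 0.018; 0.719 − 0.702 = 0.017; 0.602 − 0.583 = 0.019. With the 1.5 coding the set B differences are 0.046 and 0.043. The smaller run gives 0-0.02.
- Merging grades costs more: 0.719 − 0.563 = 0.156 and 0.602 − 0.486 = 0.116.
- Ranks minus mixed ANOVA, same design: 0.477 − 0.453 = 0.024 and 0.317 − 0.289 = 0.028; for the 1.5 coding, −0.021 and 0.003.

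**5. How often significance changes with coding.**

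- Two codings, mixed ANOVA, effect present: 9.6-10.3% (set A); 12.0% and 11.7% (set B assumptions, 300 trials each); about 9% (smaller run).
- All three codings, set B: 25.7% mid-scale and 19.2% near the floor; with no effect, 6.1% and 4.6%.
- Linear ANCOVA, three codings, effect present: 24.0% and 18.7%. Baseline adjustment alone does not remove the dependence.

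**6. Type I error.** Set B: mixed ANOVA 0.036-0.054, proportional odds 0.053-0.063. Set A: about 5-7% for all methods.

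**The case against.** The strongest case against is that MAS is one of several secondary outcomes, that section 9.1.2.3 makes the ANOVA conditional on normal data, and that coding and fallback methods for a secondary scale usually belong in the statistical analysis plan. In part this stands: the unstated coding and joint are not in themselves errors of the protocol. But the protocol does state a method for these outcomes, without exception, and that method needs a numerical spacing that the scale does not supply.

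Several stronger readings are tempting and are not supported:

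- *Treating an ordinal score as normal loses much power.* Against the same test on ranks the loss is about 0-3 points unless grades are merged. The large gap comes from the unadjusted omnibus interaction, would arise for other outcomes too, and depends on assuming an effect that peaks at Week 8.
- *The test is invalid.* Its simulated type I error is close to 5%.
- *Only a few grades can ever occur.* The limit "scores of less than or equal to level 2" applies at entry. Grades 3 and 4 remain possible at Weeks 4 and 8, and a sum over joints would have more levels.
- *An ordinal model removes the floor.* A patient at grade 0 cannot improve under any model.
- *The coding figure is a fact about this trial.* The intermediate grade is assumed; section 9.1.4.3.5 does not mention one. Without it that particular recoding does not arise, although equal spacing remains an assumption. Some disagreement near p = 0.05 is also expected of any two similar tests, as the 5-6% under no effect shows.

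**Conclusion.** The point holds in limited form. The protocol applies a normal-theory mixed ANOVA to an ordered scale, and the MAS conclusion then depends on the grade codes: roughly 10% of simulated trials with an effect change significance between two reasonable codings, and 19-26% when merging is also allowed. These figures rest on assumed distributions, an assumed intermediate grade and a single-joint score.

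Separately, replacing the interaction test with a baseline-adjusted Week 8 comparison raises power from about 0.3-0.45 (0.26-0.50 over all tabulated codings) to about 0.6-0.7. About 22-29 points of that come from adjustment and contrast, and about 0-5 from the ordinal model. The case for the ordinal model is therefore mainly that it needs no grade codes; its own power gain is small. Hypothesis 3 is affected; the Fugl-Meyer primary analysis and the sample of 165 are not. The change should be made, but it is not critical to the trial.

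**What to change.** In section 9.1.6, except MAS from the mixed ANOVA and state:

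- which joint is analysed, or a prespecified summary, or that elbow, wrist and hand are each analysed;
- a proportional-odds model of the Week 8 grade on garment, adjusted for baseline grade, or alternatively an ordinal mixed model over Weeks 4 and 8;
- common odds ratios with 95% intervals for the garment comparisons;
- mixed ANOVA at most as a sensitivity analysis, with its grade codes fixed beforehand and no merging.

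If a sum over joints is chosen, its many levels should be kept as ordered categories or the joints modelled separately, because summing again assumes spacing between grades.

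The cost is a few sentences and some extra analysis work. The proportional-odds assumption must be checked, and effects are read as odds ratios, not mean differences. Recruitment, visits and sample size do not change.

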### **9.1.7 SPIRIT Process**

SPIRIT (Standard Protocol Items: Recommendations for Interventional Trials) is a guidance document designed to provide transparency of research protocols, particularly for interventional trials. SPIRIT's goal is to ensure that trial protocols are clear, detailed, and comprehensive in order to promote the scientific validity and replicability of the study (Chan et al. 2013). The use of SPIRIT helps to ensure that trial protocols are transparent, providing investigators, reviewers, and other stakeholders with comprehensive information to enable them to understand the design and execution of the trial. This contributes to the scientific, replicable, and ethical nature of the trial (Chan et al. 2015). The SPIRIT process that will be used in this study is shown in Figure 8.

[figure not shown]

Figure 8. SPIRIT Process

**Appendix A Demographic Form (Participant)****Participant ID:****Date:**

| Demographic Form (Participant)                     |                       |
|-----------------------------------------------------------|-----------------------|
| Personal Information                               |                       |
| 1. Participant ID:                                 |                       |
| 2. Age:                                            |                       |
| 3. Gender:                                         | Male/Female    |
| 4. Hand Dominance:                                 | Right/Left     |
| 5. Affected Hand:                                  | Right/Left     |
| 6. Contact address:                                |                       |
| 7. E-mail address:                                 |                       |
| 8. Telephone number:                               |                       |
| 9. Emergency contact name:                         |                       |
| 10. Emergency contact phone number:                |                       |
| Medical Information                                |                       |
| 1. Date of stroke:                                 |                       |
| 2. Type of stroke:                                 | - Ischaemic stroke    |
|                                                           | - Haemorrhagic stroke |
| 3. Whether received pressure garment intervention: | Yes/No         |
| 4. Hours per day of occupational therapy           |                       |
| 5. Name of therapist                               |                       |
| Intervention                                       |                       |
| 1. Physiotherapy                                   |                       |
| 2. Occupational therapy                            |                       |
| 3. Traditional Chinese Medicine (TCM)              |                       |
| 4. Other treatments                                |                       |
| Lifestyle and Social Background                    |                       |
| 1. Marital status:                                 | - Single              |
|                                                           | - Married             |
|                                                           | - Divorced            |
|                                                           | - Widowed             |
| 2. Educational attainment:                         | - Primary school      |

|                                              |                           |
|----------------------------------------------|---------------------------|
|                                              | - Junior high school      |
|                                              | - High School             |
|                                              | - College                 |
|                                              | - Undergraduate           |
|                                              | - Postgraduate and above  |
| 3. Occupation:                        |                           |
| 4. Smoking history:                   | - Never smoked            |
|                                              | - Used to smoke, but quit |
|                                              | - Daily smoker            |
|                                              | - Occasional smoker       |
| 5. Drinking history                   | - Never drink alcohol     |
|                                              | - Moderate drinking       |
|                                              | - High drinking           |
| Family Status                         |                           |
| 1. Number of family members:          |                           |
| 2. Whether there is a caregiver:      | Yes/No                    |
| 3. Name of caregiver (if applicable): |                           |
| 4. Relationship to participant:       |                           |
| 5. Caregiver's contact information:   |                           |
| Additional Notes                      |                           |
|                                              |                           |

**Appendix B Fugl-Meyer Assessment**

**Appendix C Visual Analogue Scale**

**Participant ID:**  
**Date:**

Visual Analogue Scale(VAS)

No pain

unbearable pain

**Appendix D Disabilities of the Arm, Shoulder and Hand**

:

**Appendix E Box and Block Test Result Form**

**Box and Block Test**

**Participant ID:**  
**Date:**

|            |             |
|------------|-------------|
|            | unit (units |
| Left Hand  |             |
| Right hand |             |

**Appendix F Modified Ashworth Scale**

**Appendix G SF-36 Questionnaire**

**Appendix H Brunnstrom Recovery Stage**

## Appendix I1 SLUMS Examination

## Appendix J Pressure Garment Application Form

**Participant ID:**

**Date:**

| Pressure
Garment
Application
Form | Date | Time of
use
(daytime) | Time of
use
(night) | Treatment
Frequency | Treatment
Duration | Treatment
Location | Name of
therapist | Carer's
participation | Remarks |
|------------------------------------------------------|------|-----------------------------|---------------------------|------------------------|-----------------------|-----------------------|----------------------|--------------------------|---------|
|                                                      |      |                             |                           |                        |                       |                       |                      |                          |         |
|                                                      |      |                             |                           |                        |                       |                       |                      |                          |         |
|                                                      |      |                             |                           |                        |                       |                       |                      |                          |         |
|                                                      |      |                             |                           |                        |                       |                       |                      |                          |         |
|                                                      |      |                             |                           |                        |                       |                       |                      |                          |         |
|                                                      |      |                             |                           |                        |                       |                       |                      |                          |         |
|                                                      |      |                             |                           |                        |                       |                       |                      |                          |         |
|                                                      |      |                             |                           |                        |                       |                       |                      |                          |         |
|                                                      |      |                             |                           |                        |                       |                       |                      |                          |         |
|                                                      |      |                             |                           |                        |                       |                       |                      |                          |         |
|                                                      |      |                             |                           |                        |                       |                       |                      |                          |         |
|                                                      |      |                             |                           |                        |                       |                       |                      |                          |         |
|                                                      |      |                             |                           |                        |                       |                       |                      |                          |         |
|                                                      |      |                             |                           |                        |                       |                       |                      |                          |         |

